## Abstract

**Background:**

Over the last years, living kidney donation (LKD) has been established for patients with endstage renal failure as an alternative to post mortem donation, which is limited by organ scarcity and long lasting waiting periods. From an ethical perspective, the increase in LKD requires that donors’ physical, psychological, and social harm has to be minimized as much as possible and the risk should not exceed the generally expected consequences of nephrectomy. Despite of numerous, mainly retrospective studies about the postoperative outcome of LKD over the last years from different countries, it becomes apparent that there is a lack of comprehensive prospective multicenter research in this field worldwide. Therefore, the main aim of the study is to examine the physical and psychosocial outcome of living kidney donors in a prospective design before and after transplantation in an interdisciplinary approach (surgery, nephrology, psychosocial medicine).

**Methods/design:**

The goal of the study is to investigate such aspects as the impact of gender- and age-specific factors on LKD outcome, donor outcome in correlation to the health status of the recipient, the medical and psychosocial risk of a healthy subject undergoing the LKD procedure. The study is carried out as a nationwide multicenter study. All adult living kidney donors with sufficient knowledge in the German, Russian, or Turkish language, informed consent, and place of residence in Germany are included. In a naturalistic design (cohort study), clinical data and self-report measures (questionnaires) of 320 donors are collected before and 8 weeks, 6 and 12 months after donation. Primary outcome parameters are the kidney function (estimated GFR) and the quality of life (SF-36) of the donor. Secondary outcome parameters are data about physical (e.g., wound healing, blood pressure) and psychosocial (fatigue, depression, anxiety, somatization) outcome after donation.

**Discussion:**

Previous studies on the postoperative outcome of living kidney donors have methodological limitations and/or were carried out in countries with different healthcare systems, e.g. United States, Norway, Canada, United Kingdom. Thus, results cannot be generalized and are not particularly applicable to the risks of mainly caucasian living kidney donors in the German healthcare system. The study design overcomes these disadvantages in that it provides a prospective multicenter design.

**Trial registration:**

German Clinical Trials Register DRKS00006552 (22 September 2014).

## Background

For patients with endstage renal disease (ESRD), transplantation is currently the only treatment to regain an adequate renal function. Post mortem donation normally requires a long waiting time for the transplant recipient, due to the limited availability of organs. The actual waiting time in Germany is 6–7 years according to the German Organ Transplantation Foundation (Deutsche Stiftung Organtransplantation, https://www.dso.de/). Therefore, LKD has become an established alternative in recent years, which has many advantages for the kidney recipient. The transplantation can be done preemptively and is associated with a better rate of survival of the transplanted kidney as well as the organ recipient [1, 2]. Quality of life (QoL) and life expectancy of the kidney recipient are improved and the occurrence of cardiovascular complications is reduced [3, 4]. Furthermore, a faster rehabilitation and a better reintegration into the daily activities and the occupational life contribute to reduce healthcare costs by € 280.000 compared to continuing dialysis treatment [5]. Worldwide the percentage of LKDs among all kidney transplantations varies widely due to the scarcity of organs from post mortem donors (KDIGO Guideline Evidence Report) [6]. In Germany, approximately 30% (living donors *n* = 645 / post mortem *n* = 1550) of all performed kidney transplantations were done with a living donor organ in 2015 (statistics.eurotransplant.org).

The German transplantation law requires that living donors should not be put at excessive risks due to the operation or its consequences. Relatively few published studies examined the surgical, general health, and psychosocial risks of donors following donation, most being retrospective in design. Older studies did not find an increased risk of advanced renal failure or of a relevant decline in glomerular filtration rate (GFR) in kidney donors compared to the general population [7–10]. In contrast, recent publications from registers in the US and in Norway reported a less favorable renal outcome among living kidney donors compared to a control group of potential donors from the healthy population [11, 12]. The position paper of the European Committee on Organ Transplantation (CD-P-TO) criticized these studies because of their methodological limitations and listed a series of evidence, which contradict the results of both studies [13]. With relation to comorbidities, studies examining other outcomes, such as the impact of hypertension [14–16] or obesity [17] are scarce and also report conflicting results.

There are no prospective randomized multicenter studies on the psychosocial long-term risks and consequences for donors. Frade et al. examined QoL in donors before and after (18,8+/− 12,8 months) donation and found only one significant improvement after donation of social functioning scores (from 79.1 to 89.8). The other SF-36 subscales remained unchanged [18]. Another study showed that living kidney donors after donation (on average 32 months) scored significantly better among the SF-36 scales “social functioning,” “bodily pain,” and “vitality” compared to the controls (healthy population) or to patients with renal tumors [19]. Some other studies, however, found that QoL was significantly reduced in the areas of physical [20–25] or mental health related [26, 27] components of QoL within the first post-operative period (up to 6 months). Most of these reductions were no longer found, however, at later measurement points. Some studies showed increased pain and fatigue within the first weeks after surgery and a higher incidence of mental disorders during the first 12 months postoperatively [20, 26, 28]. Important limitations of prior prospective studies included small sample sizes, monocentric conduction and the neglecting of the health status of the recipient as possibly influencing the donor’s well-being. Further limitations include a lack of gender-specific aspects [29, 30] and the problem of limited transferability of results to other countries due to differences in the healthcare systems.

Aim of the SoLKiD study (“Safety of Living Kidney Donors”) is to examine physical and psychosocial outcomes of living kidney donors based on a prospective multicenter design, an integration of relevant disciplines (surgery, urology, internal medicine, nephrology, psychosocial medicine), a detailed assessment of the psychosocial status at several time points, and additionally taking the recipient’s health status into account.

## Methods/design

### Study centers

The study is carried out at 20 transplant centers in Germany. Participating centers are the University Hospitals of RWTH Aachen, Campus Charité Berlin Mitte, Campus Charité Berlin Virchow, Dresden, Düsseldorf, Essen, Frankfurt, Giessen, Hamburg-Eppendorf, Heidelberg, Halle (Saale), Schleswig-Holstein Campus Kiel, Schleswig-Holstein Campus Lübeck, Köln, Mainz, Mannheim, Münster, Würzburg, Westpfalz-Klinikum Campus Kaiserslautern, and Hannover Medical School. Donor-recipient pairs are recruited in the respective outpatient departments of the hospitals after signing informed consent. Study coordination is done at the University Hospital of Münster. The study is performed in accordance with the declaration of Helsinki and with the local ethics committees of all participating centers.

### Participants

Inclusion and exclusion criteria for living kidney donors are listed in Table 1.

**Table 1 Tab1:** Inclusion and exclusion criteria of the SoLKiD study for living kidney donors

Inclusion criteria	• Living kidney donors before upcoming nephrectomy
	• Age > 17 years
	• Informed consent
	• Native language German, Turkish, Russian
Exclusion criteria	• Refusal to participate
	• Not living in Germany
	• Lack of reading comprehension in the native language

As a common consensus between the participating centers, the Russian-speaking and Turkish-speaking donors are included in the study in addition to German-speaking donors, as they constitute a representative part of the population in Germany and because validated questionnaires in Turkish and Russian language are available. The study started in 2014 and included 320 donors for the baseline assessment prior to transplantation, corresponding to approximately 50% of the annually conducted living donations in Germany. With an expected follow-up rate of > 80%, approximately 260 participants can be followed up to 1 year after donation.

### Measurement time points

Living kidney donors and the associated organ recipients are examined at four time points (T0, T1, T2, T3) before donation and during the regular follow-up visits required by the transplant centers. All data for the baseline assessment (T0) is collected immediately (1–2 days) before the donation in order to avoid in the case of the earlier baseline assessment (e.g. during the preparation process for the donation) the possible donors’ concern that they might be considered as not suitable for donation because of their answers. The data collection for all time points corresponds with the clinical routine process and is imbedded into the usual care practice of LKD. The time points of measurement of the study are shown in Fig. 1.

**Fig. 1 Fig1:**

Time points of measurement in the SoLKiD study

### Study measures: Primary and secondary outcome variables

Data are collected by the transplant centers within the usual donor and recipient preparation and care. They include laboratory values ​​(serum creatinine, eGFR, proteinuria, blood sugar levels), and clinical data (blood pressure, weight, surgical complications). In addition, further information, in particular psychosocial status variables, are collected by means of questionnaires at four time points. Questionnaires used in the study are listed in Table 2.

**Table 2 Tab2:** Questionnaires used in the SoLKiD study for living kidney donors

Questionnaire	Short description	Scales
SF-36 [45, 46] (Short-Form 36-Item Health Survey)	Standardized, generic instrument for the detection of health-related quality of life in the general population and in different patient groups. 8 dimensions can be conceptually summarized in two components: “physical health” and “mental health”.	Physical functioning, physical role function, bodily pain, general health, vitality, social functioning, emotional role function, and mental health; summary scales: physical health summary score, mental health summary score
MFI [47, 48] (Multidimen-sional Fatigue Inventory)	Standardized self-assessment tool that measures perceived tiredness (fatigue) in extent, nature, and intensity. The values can be compared inter- and intra-individually.	General fatigue, physical fatigue, reduced activity, reduced motivation, mental fatigue
PSS-10 [49] (Perceived Stress Scale)	Instrument for the measurement of the subjective stress rating and evaluation of the global perceived stress. It measures a degree of frequency, how the answerers grade their lives as unpredictable, uncontrollable, and overburdening.	Global degree of frequency of perceived stress
PHQ-D Short Form [50] (Patient Health Questionnaire)	The questionnaire was developed to facilitate the detection and diagnosis of the most common mental disorders in primary medicine. In addition to questions about mental disorders, there are also items for psychosocial function ability, stressors, critical life events and - for women - menstruation, pregnancy, and childbirth. In addition to the categorical diagnosis of mental disorder, severity ratings for the areas depression, somatic symptoms and stress can be provided (continuous diagnostics).	The short form, which is used in the present study, refers to the following scales: Depression (PHQ-9); Anxiety (GAD-7); Somatization (PHQ-15). For these scales, the formation of a separate scale for each point value (scores) for measuring the severity is possible.
CERQ [51, 52] (Cognitive Emotion Regulation Questionnaire)	Instrument for detecting the different components of habitual cognitive emotion regulation. It comprises nine dimensions, which measure the possible mental responses to an aversive event and thus triggered emotions.	Catastrophizing, self-blame, rumination or focus on thought, positive reappraisal, positive refocusing, refocusing on planning, other-blame, putting into perspective, acceptance

Estimated GFR (eGFR) using the CKD-EPI creatinine equation [31] of the donor and the physical and mental summary scores of the SF-36 are defined as primary outcome variables. All other outcomes of the physical and mental health status of the donor are used as secondary outcomes.

Psychosocial consequences for a donor can either be assessed as a reduction in the mental health score of the SF-36, or as an increase in depression or anxiety scores, or as an increase in scores for somatization (PHQ-D), change in psychosocial functioning and increased stress (PSS-10) or fatigue (MFI). Additionally, at baseline different components of a habitual cognitive emotion regulation scale (CERQ) are assessed, enabling a control of the relationship between the present ability of adequate emotion regulation and postoperative psychosocial consequences in donors.

Psychosocial variables which reflect the current mental state of donors additionally include the subjective attitude towards donation and the assessment of donor-specific relationship aspects to the recipient. This includes, for example, if a donor would donate again, or if he/she felt him/herself to be pushed towards donation by others. All questionnaires are offered either in German, Russian or Turkish validated versions. Information is collected independently from donor and from recipient to avoid a two-way influence during the assessment. The standardized assessment form with the clinical data of donors and recipients plus the donor questionnaires are sent in a pseudonymized manner to the data management center in Münster at all four time points.

### Statistical analysis

Statistical analyses will be performed according to the principles of the ICH-guideline E9 “Statistical Principles for Clinical Trials” using standard statistical software.

A detailed description of the study population will be given using summary statistics such as mean and standard deviation, median and quartiles, or absolute and relative frequencies, as appropriate.

Each of the three co-primary outcomes, i.e. the donors’ eGFR and QoL according to the SF-36 “physical health” and “mental health” summary score will be analyzed using a *Mixed Linear Model*. This method is chosen in order to account for repeated measurements of individual donors’ outcomes over time (longitudinal data). One important advantage of the *Mixed Model* approach is that missing values in outcomes are handled in a way that prevents biased results. In the established models, all relevant independent variables will be included that impact the respective outcome, first of all the baseline values of the respective outcomes. Furthermore prognostic factors as gender, age, and education will be included in the model in order to adjust for confounding. Basic model assumptions such as the Gaussian distribution of model residuals will be checked using graphical methods, including histograms and quantile-quantile plots. If necessary, outcome variables will be transformed appropriately, applying square-root, logarithmic or *Box-Cox* transformations. Models will be fitted using *Restricted Maximum Likelihood* methods. Model selection will be performed using stepwise variable selection methods based on *Akaike’s* information criterion. Final models will be validated by diagnostic checks including the calculation of goodness of fit statistics and the examination of the randomness of model residuals. The model’s predictive performance will be checked using *cross-validation*.

In the primary statistical analysis, the following hypothesis test problems are established in an analogous manner in case of each of the three co-primary outcomes eGFR, SF-36 “physical health” and “mental health” summary score. Denote μ_i_ (*i* = 1,2,3) the expected values of the respective outcome at three consecutive follow-up visits T1, T2, and T3. The global null hypothesis H_0_:μ_1_ = μ_2_ = μ_3_ is established and tested against the alternative H_1_:∃(i,j)∈{1,2,3}: μ_i_ ≠ μ_j_ in order to detect any kind of mean changes over time. Beyond the global null hypothesis, pairwise comparisons of expected values μ_i_ (i = 1,2,3) are performed by testing the null hypotheses H_0_^(12)^: μ_1_ = μ_2_, H_0_^(13)^: μ_1_ = μ_3_ und H_0_^(23)^: μ_2_ = μ_3_ against the corresponding two-sided alternatives. The overall multiple significance level across the three co-primary outcomes is set to α = 0.05. In order to keep this significance level, Bonferroni adjustment is applied. Each of the three co-primary outcomes is assigned the local significance level α_loc_ = 0.05/3 = 0.0167, i.e., α_loc_^eGFR^ = 0.0167, α_loc_^SF36phys^ = 0.0167 and α_loc_^SF36mental^ = 0.0167. Within each of the three co-primary outcomes, the following multiple testing strategy is applied, that is derived from the closed test principle. Denote the calculated *p*-values of the pairwise null hypotheses H_0_^(ij)^: μ_i_ = μ_j_ (i,j∈{1,2,3}) p_ij_ and the p-value of the global null hypothesis H_0_:μ_1_ = μ_2_ = μ_3_ p_123_. Any specific pairwise null hypothesis H_0_^(ij)^ is rejected if and only if both p_ij_ ≤ 0.0167 and p_123_ ≤ 0.0167. This multiple testing strategy provides strong control of the family-wise type I error rate α_loc_ = 0.0167. Each of the above null hypotheses will be tested using *Wald* type tests of the respective contrasts in the final established *Mixed Linear Model*. Point estimators of all contrasts will be supplemented by (two-sided) confidence intervals. The primary efficacy analysis provides confirmatory statistical evidence. Secondary outcomes will be analyzed using descriptive and inferential statistical methods. Appropriate tests will be applied for pre-specified hypotheses. Point estimates and associated 95% confidence intervals will be provided.

Further exploratory and safety analyses will be performed. In exploratory and safety analyses, no correction for multiplicity will be applied. An overall or multiple significance level is not determined and cannot be calculated. Results are regarded noticeable in case *p* ≤ 0.05, and are interpreted, accounting for the relatively low level of scientific evidence.

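### Strong type I error control is claimed for tests in a stepwise-selected model with an open candidate set, so it is not assured as written

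*Protocol article*

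**What the plan says.** In the protocol article (Methods/design, Statistical analysis), each co-primary outcome is analysed with a mixed linear model: eGFR and the SF-36 physical and mental summary scores. Every relevant explanatory variable with an influence on the outcome is to enter, beginning with that outcome's own baseline value. On named covariates the text says "Furthermore prognostic factors as gender, age, and education will be included in the model". Two adjacent sentences then read "Models will be fitted using *Restricted Maximum Likelihood* methods" and "Model selection will be performed using stepwise variable selection methods based on" Akaike's information criterion. The section does not say which likelihood feeds the criterion. Nor does it say whether candidates may be measured after donation or may interact with visit.

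The next paragraph sets the tests. The hypotheses concern the expected outcome at T1, T2 and T3: a global null of equality, then three pairwise nulls tested "against the corresponding two-sided alternatives". It states that "The overall multiple significance level across the three co-primary outcomes is set to α = 0.05" and that "Each of the three co-primary outcomes is assigned the local significance level" 0.05/3 = 0.0167. A pairwise null is rejected only if its own p-value and the global p-value are both at most 0.0167. Of this rule the text says "This multiple testing strategy provides strong control of the family-wise type I error rate". The tests are Wald "type tests of the respective contrasts in the final established" mixed model, and the analysis is called confirmatory.

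**The concern.** A closed test controls error when each component test has its nominal level. Wald tests in a model fixed in advance have it, approximately. Wald tests in a model that the same data chose do not have it automatically, and the text makes no allowance for the choice.

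The candidate set is also unbounded. Under Study measures, questionnaires are collected at all four time points, so post-donation fatigue, stress and depression scores are at hand and are plausible correlates of the SF-36. If such a variable enters, the visit contrast is adjusted for something that itself changes over visits, and it no longer addresses the stated hypothesis about mean outcomes.

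At stake is whether the three co-primary results can be reported as confirmatory at the stated level.

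**Working it through.** **1. The plan's own figure.** 0.05/3 = 0.0167 per outcome, and 3 × 0.0167 = 0.05. This reproduces.

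**2. The closed test in a fixed model.** With three means, any two pairwise nulls together imply the global null. The closure therefore contains only the global null and the three pairwise nulls, and requiring both p-values to be at most 0.0167 is a valid closed test. The rule is sound. The open question is the model in which it is applied.

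**3. Error after selection.** From the documents: 200 evaluable donors, visits T1 to T3, local level 0.0167, the global-then-pairwise rule. Assumed: random-intercept data with equal true visit means; T0 value, gender, age and education forced in; eight time-constant noise candidates; in some settings six further time-varying candidates, or visit interactions with six binary covariates. No candidate truly affects the outcome. Selection is stepwise by AIC and the final fit is REML. There were 3,000 runs per setting, with Monte Carlo standard error √(0.0167 × 0.9833/3000) = 0.0023. Family-wise error per outcome:

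| Eligible for selection | No selection | ML-AIC | REML-AIC | REML-AIC, candidate columns × 0.1 |
|---|---|---|---|---|
| Time-constant main effects | 0.019 | 0.020 | 0.020 | 0.020 |
| Same, with missing visits | 0.014 | 0.015 | 0.014 | 0.014 |
| Time-varying, no trend | 0.019 | 0.020 | 0.018 | 0.019 |
| Time-varying, trending over visits | 0.019 | 0.038 | 0.018 | 0.025 |
| Visit interactions, uncentred | 0.021 | 0.082 | 0.023 | 0.071 |
| Visit interactions, centred | 0.021 | 0.021 | 0.021 | 0.021 |

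The pattern has a simple reason. The tests are within-donor contrasts, and a time-constant main effect carries almost no information about them. A trending candidate is correlated with visit, so a chance association that gets it selected also shifts the visit contrast. With an uncentred interaction the visit coefficient becomes the contrast in the reference category, and the interaction is selected because subgroups differ by chance.

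If the visit term is itself a candidate (2 df), AIC keeps it when the likelihood-ratio statistic exceeds 4, that is p < exp(−2) = 0.135. Rejection at 0.0167 needs −2 ln(0.0167) = 8.19. That step alone adds no false rejections.

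**4. What the adjusted contrast tests.** With a time-varying covariate Z in the model, the T3–T1 contrast is (μ₃ − μ₁) − β × (mean change in Z). Equal outcome means make this zero only if β or the mean change in Z is zero. Assumed example: outcome SD 8, within-donor correlation −0.4 with fatigue, both variables having the same within-donor share of variance, and fatigue falling 0.5 SD. Then β = −0.4 × 8 = −3.2 per SD of fatigue, and the contrast is 0 − (−3.2) × (−0.5) = −1.6 units although μ₁ = μ₃.

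**5. The criterion.** In its usual form the REML likelihood includes log det(X′V⁻¹X). Multiplying one covariate by c moves the REML-based AIC by 2 ln c. Age in months instead of years gives 2 ln 12 = 4.97, against a penalty of 2 for one coefficient; ML-based AIC does not move. In one simulated data set (200 donors, three visits) the change in AIC attributed to age was 1.55 in decades, 6.16 in years and 11.13 in months under REML, and 1.86 in every unit under ML. In the first row of the table, REML-AIC kept on average 0.02 noise columns, and 0.33 when the same columns were multiplied by 0.1. ML-AIC kept 1.34.

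**The case against.** **The covariates actually named are harmless.** T0 value, gender, age and education are time-constant. Fatigue and blood pressure are classed as secondary outcomes, and the one psychosocial scale offered for control, the CERQ, is taken at baseline. This stands, and it limits the finding: a reader might infer that type I error control fails, and the documents do not support that. Inflation needs candidates that the text neither names nor excludes. What remains is an unqualified claim over an unbounded set.

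**The analysis plan is not shown and may list the candidates.** True, and a list there could settle the matter. But the article does not merely stay silent. It states data-driven selection and rests the confirmatory tests on its result.

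**AIC on REML likelihoods is inferred.** Correct. Comparing fixed effects by ML and refitting by REML is compatible with the text. A reader might also infer that a REML-based criterion is what breaks the error rate. The table says otherwise: at unit scale REML-AIC stayed at 0.014 to 0.023, because it kept almost nothing, while ML-AIC gave the larger figures. The unit dependence is a separate fault, and a conditional one.

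**A much larger figure can be produced.** In the fatigue example, extended to correlations of 0.3 to 0.5 in size, equality of visits is rejected in about 30% to 88% of runs although the outcome means are equal. That is conditional on the covariate being in the model and on the assumed trend. It would arise equally if the covariate had been pre-specified. It measures a change of estimand, not inflation from stepwise selection.

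**Gender, age and education.** A reader might see a contradiction between promising these covariates and then selecting variables. The promise reads naturally as forcing them in, with selection applied to the rest. Nor is it an error in itself that the three outcomes could end with different covariates.

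**Conclusion.** The concern holds in a limited form. The claim of strong control at 0.0167 is justified for a fixed model, whereas the plan applies it to a selected one, so control is not assured as written. If only time-constant main effects are eligible, the effect is negligible, also with missing visits. If trending post-donation variables or uncentred visit interactions are eligible, the error per outcome can reach about 0.04 to 0.08 with ML-AIC. Those figures rest on assumed effects, variances and numbers of candidates. Adjusting for a trending post-donation covariate also replaces the stated hypothesis by a different one, whatever the selection method. If AIC comes from the REML fits, it cannot rank models with different fixed effects.

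**What to change.** Pre-specify the confirmatory model for each co-primary outcome: categorical visit, T0 value, age, gender, education and a stated within-donor covariance structure, fitted by REML. Allow no variable selection and no post-donation covariates. Run the global and pairwise Wald tests there. In the simulation the fixed model had an error of 0.014 to 0.021, which is nominal within Monte Carlo error. Keep stepwise AIC and cross-validation for exploratory prognostic models, and state that fixed effects are compared there by ML.

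If selection has to stay in the primary analysis, limit the candidates to time-constant pre-donation main effects, say that visit and the named covariates are exempt, and compute AIC by ML.

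The cost is a change of wording and a few degrees of freedom, which is minor with about 200 donors.

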### Sample size calculation

The necessary number of study participants follows from the anticipated effects in the three co-primary outcomes. In Gossmann et al. [7], the observed mean eGFR was 92 mL/min/1.73m^2^ before and 71 mL/min/1.73m^2^ after donation (relative difference |Δrel| ≈ 23%), each with a standard deviation of 15–20 mL/min/1.73m^2^. Similar results were obtained in the study by Ibrahim et al. [9]. In Kroencke et al. [21], average SF-36 “physical health” summary scores were observed at successive measurement time points, that vary between 51 and 56 units (|Δrel| ≈ 10%), each with a standard deviation of up to 8 units. The SF-36 “mental health” summary score amounted to around 53 units and relatively stable in time, with standard deviations of 6.3, 8.9 and 7.7 units at the three consecutive measurement time points. Similar results were obtained in the retrospective study of Wiedebusch et al. [32], who reported SF-36 summary scores of 51–52 units with a standard deviation of 9 units 6 months after surgery. In case of all outcomes, measures obtained from an individual study participant at successive measurement time points are assumed to be positively correlated. A total number of 320 pairs of kidney donors and recipients will be included in the study, resulting in 2 × 320 = 640 study participants. A number of 200 pairs of kidney donors and recipients is expected to provide evaluable data. With this sample size, the above reported differences in the co-primary outcomes eGFR and SF-36 “physical health” summary score can be detected with a power of > 90% in the primary statistical analysis. For the third co-primary outcome SF-36 “mental health” summary score, possible mean differences between successive measurement time points in the order of 3 units (|Δrel| ≈ 6%) can be detected with a power of > 85%. Power calculations were performed using the SAS software.

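### The confirmatory tests compare only the three post-donation visits, so change from before donation is not tested confirmatorily, and the eGFR power claim refers to a contrast that the primary analysis does not contain

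*Protocol article*

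**What the plan says.** All references are to the protocol article.

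- **Aim.** The Abstract (Background) says the main aim is to "examine the physical and psychosocial outcome of living kidney donors in a prospective design before and after transplantation".
- **Schedule.** The Abstract (Methods/design) says the data "are collected before and 8 weeks, 6 and 12 months after donation". Measurement time points adds: "All data for the baseline assessment (T0) is collected immediately (1–2 days) before the donation". So T0 is the only pre-donation visit.
- **Model.** Statistical analysis specifies a mixed linear model for each of the three co-primary outcomes. Its independent variables are to include "first of all the baseline values of the respective outcomes".
- **Hypotheses.** The same section defines the three means as "the expected values of the respective outcome at three consecutive follow-up visits T1, T2, and T3". The global null is that they are equal, and it is tested "in order to detect any kind of mean changes over time". The only pairwise nulls are T1 against T2, T1 against T3 and T2 against T3, each tested "against the corresponding two-sided alternatives". A pairwise null is rejected when its own p-value and the global p-value are both at most 0.0167. This analysis is described as the confirmatory one.
- **Power.** Sample size calculation cites a study in which "the observed mean eGFR was 92 mL/min/1.73m^2^ before and 71 mL/min/1.73m^2^ after donation". It states that 200 evaluable pairs give more than 90% power for that difference in the primary statistical analysis.

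**The concern.** The interval that contains the operation lies outside every confirmatory contrast. The tests ask whether the course between week 8 and month 12 is flat. They do not ask whether donors differ from their own state before donation.

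This can mislead in two directions. A large loss that is stable from week 8 satisfies the null and gives no confirmatory finding. A drop at T1 that only partly recovers can reject the null and be reported as a rise over time, while donors are still below T0 at 12 months. The statement about recovery would be true, but without T0 it does not show whether harm remains.

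The power statement adds a plain inconsistency: the effect that justifies the sample size for eGFR cannot appear in the analysis it is said to power.

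**Working it through.** **Inputs from the Statistical analysis and Sample size sections.** Two-sided level per outcome 0.05/3 = 0.0167 (critical z = 2.394); n = 200 evaluable donors; eGFR 92 before and 71 after, SD 15–20; SF-36 physical scores between 51 and 56, SD up to 8; SF-36 mental difference 3 units, SDs 6.3, 8.9 and 7.7 (about 9 in a second source). Correlation within donors is said to be positive, with no value. I assume r = 0 as the unfavourable case and show higher values where they matter.

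**1. The plan's power figures.** For a paired contrast, SE = √[(s₁² + s₂² − 2·r·s₁·s₂)/n], with power from the noncentral t distribution. At r = 0:

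| Outcome | Difference | SDs | SE | Difference/SE | Power |
|---|---|---|---|---|---|
| eGFR | 21 | 20, 20 | √(2·20²/200) = 2.0 | 10.5 | >0.999 |
| SF-36 physical | 5 | 8, 8 | √(2·8²/200) = 0.8 | 6.25 | 0.9999 |
| SF-36 mental | 3 | 6.3, 7.7 | 0.70 | 4.26 | 0.967 |
| SF-36 mental | 3 | 6.3, 8.9 | 0.77 | 3.89 | 0.929 |
| SF-36 mental | 3 | 8.9, 7.7 | 0.83 | 3.60 | 0.882 |
| SF-36 mental | 3 | 9, 9 | 0.90 | 3.33 | 0.820 |

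The stated bounds (>90%, >90%, >85%) hold as arithmetic. The one row below 85% needs SD 9 at both visits and no correlation; r = 0.1 already gives 0.863. The fault is therefore not the size of the trial. The eGFR figure belongs to a contrast between T0 and a later visit, and the primary analysis has none.

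**2. The stated test under the plan's own eGFR figures.** Take T0 = 92 and T1 = T2 = T3 = 71, SD 20. The global test depends on λ = n·(Cμ)′(CΣC′)⁻¹(Cμ), where C holds the differences among T1, T2 and T3. With equal means Cμ = 0, so λ = 0 and the rejection probability is the level itself, 0.0167, at every correlation (checked at r = 0, 0.3, 0.5 and 0.7). A test that includes T0, or the T3–T0 contrast alone, has power above 0.999. For SF-36 physical with a lasting drop from 56 to 51 (SD 8, r = 0.5), the results are again 0.0167 and above 0.999.

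**3. What the stated eGFR test can see.** For a linear drift across T1 to T3, with SD 20 and n = 200:

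| Drift T1 to T3 | r = 0 | r = 0.5 | r = 0.8 | r = 0.9 |
|---|---|---|---|---|
| 2 units | 0.06 | 0.11 | 0.33 | 0.67 |
| 5 units | 0.42 | 0.79 | 0.997 | >0.999 |

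The claim of more than 90% for 21 units says nothing about changes of this size.

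**4. Does the baseline covariate supply the missing test?** Entered as a main effect, the baseline value shifts the adjusted means at T1, T2 and T3 by the same amount, which cancels in every contrast among them.

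**5. Extending the present rule to four means.** Suppose T0 differs strongly and T1 = T2 = T3. The global null is then rejected almost surely and stops protecting the pairwise tests. The three true pairwise nulls are each tested at 0.0167, so at least one is falsely rejected when the studentized range of three means exceeds 2.394·√2 = 3.386. That probability is about 4.4%; a simulation gave 4.3%. The nominal level is 1.67%.

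**The case against.** A reader might infer that the effect of donation is never tested anywhere. The document does not support that. Statistical analysis announces further exploratory and safety analyses, and an analysis plan that is not shown may hold T0 contrasts. The gap is in the confirmatory family. It is still a gap: secondary outcomes are defined as variables other than the three primary ones, and the article itself gives exploratory results a low level of evidence.

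The aim also has two parts. The Discussion speaks of outcomes during the 12 months after nephrectomy and of the natural course, and the T1–T3 tests serve that part. The same paragraph asks which health risks follow removal of a kidney, and those tests do not answer it.

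The model is not wrong in itself. With baseline as a covariate, change from T0 can be estimated if the sampling error of the mean baseline is included. What is missing is the contrast.

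For eGFR, a test of zero change is close to a certain rejection on the plan's figures, so its p-value says little. This stands, and it is why the size of change with its confidence interval matters. The same nulls apply to both SF-36 scores, where the Background describes conflicting results.

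Finally, it is tempting to say that the SF-36 physical power is mismatched as well. The article does not say whether a pre-donation visit is among the time points that gave 51 to 56, so the mismatch is certain only for eGFR.

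**Conclusion.** The point holds for the confirmatory analysis. For all three co-primary outcomes, no confirmatory contrast compares any visit with the state before donation, although that comparison is part of the stated main aim. Statistical analysis and Sample size calculation contradict each other on eGFR: on the plan's own means, with no later change, the primary test rejects with probability 0.0167 and not more than 0.90.

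The missing contrast is affordable at n = 200. At r = 0, power is above 99.9% for eGFR, about 99.99% for SF-36 physical and about 0.82 to 0.97 for SF-36 mental; positive correlation raises all three. The SF-36 physical figure assumes that the 5 units apply before against after donation, and the SF-36 mental figure assumes the same for 3 units.

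**What to change.** Amend the protocol and analysis plan as follows.

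1. **Add T0 to the confirmatory contrasts.** Either make T0 a response level in the mixed model, with visit as a four-level factor and baseline dropped as a covariate, or analyse change from T0 adjusted for baseline, allowing for the sampling error of the baseline mean. Both are valid; choose one in advance.
2. **Test at least T3–T0 at 0.0167 for each outcome.** Take T2–T0 and T1–T0 in a pre-specified fixed sequence, or use a full closed test with all intermediate intersection hypotheses. Do not extend the present global-plus-pairwise rule to four means.
3. **Report the size of each change with its confidence interval**, above all for eGFR. When interpreting SF-36, note that T0 is taken 1–2 days before surgery.
4. **Keep the T1–T3 comparisons as secondary**, to describe the course after donation.
5. **Restate the power section** so that each difference is tied to the contrast that tests it.

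**Cost.** No new data are needed, because T0 is already collected. The T1–T3 pairwise tests lose confirmatory status. The Participants section says that recruitment began in 2014 and that 320 donors were included at baseline, so the change needs a documented, dated amendment made without knowledge of the outcome data. If outcome data have already been seen, the T0 contrasts should be labelled as added afterwards.
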